### Patient and public involvement

Extensive PPI work underpins this study. Motiv8 has been co-developed and co-produced with service users and staff, from conception and ongoing iterative updates have been used to incorporate feedback from previous cohorts. Multiple discussion groups and consultations have been held with service users in secure services to refine the protocol and inform the design pre- and post-funding allocation. All research materials, such as information sheets, branding materials and recruitment leaflets have been co-produced with service user input. The core research team consists of investigators with lived experience and parent/carer representatives. PPI representatives will ensure the research is appropriate and sensitive to the needs of service users. People with lived experience will assist with the delivery of the intervention and provide peer support. Following the award of the grant, an independent expert by-experience group has been set up consisting of people who have previously used secure services. This group meets bimonthly and will continue to advise on all aspects of study progress (e.g. recruitment, analysis, and dissemination).

### Progression criteria

A red/amber/green criterion for progression to a full trial will be used, with a stop/refine/go approach. This will likely be recruitment > 80% (green), 60–79% (amber), < 60% (red) of planned target; adherence > 70% (green), 50–69% (amber), < 50% (red) attendance at planned sessions; retention within the study > 75% (green), 60–74% (amber), < 60% (red) completion of proposed primary outcome for the definitive trial (weight). Retention to the proposed primary outcome measure for a definitive trial (change in weight) will be monitored.

## Ethics and dissemination

### Ethics and dissemination

The trial has received Health Research Authority (HRA) approval (IRAS 299909) from the London–Bromley Research Ethics Committee (25th October 2021, 21/LO/0658). Local capacity and capability to deliver the research will be provided by the research department at the sponsoring organisation, Greater Manchester Mental Health NHS FT. Dissemination will occur with researchers, staff, service users and PPI representatives. Outputs and results of the trial will be published in open-access, peer-reviewed international journals where possible. Authorship will follow International Committee of Medical Journal Editors guidance (ICMJE | Recommendations | Defining the Role of Authors and Contributors). To increase reach, results will also be disseminated with the help of PPI input to non-academic audiences via media posts, blogs, newsletters and written summaries created with PPI groups. Summaries and updates will be presented to healthcare providers, managers and commissioners and shared via healthcare professional networks to ensure maximum reach. Results will be disseminated via local and international conferences and shared across social networks.

### Adverse events

Serious Adverse Events (SAEs) are untoward medical occurrences that result in death, are life-threatening, require inpatient hospitalisation or prolongation of existing hospitalisation or result in persistent or significant disability. For this study, other ‘important medical events’ are considered as adverse events such as serious violent incidents, or increased security status. SAEs are expected throughout the study period, such as incidents of self-harm, or violence and aggression. Exercise sessions form part of the intervention and therefore, adverse reactions such as muscle soreness and injury are more likely during the study period. Strategies to mitigate these risks have been incorporated into the study protocol (e.g. supervised sessions, graded increase in exercise). A trial standard operational procedure has been created to ensure all SAEs which are reported to the research team are assessed and categorised in line with HRA requirements. The research team, TSC, and experts by experience group will be made aware of any SAEs and will determine whether they are related to participation in the trial. Immediate safety concerns will be addressed as soon as possible with strategies put in place to prevent further risk to participants. Clinical notes will be reviewed at the end of the study period and any SAEs will be recorded if deemed relevant to participation. Adverse events will be reported in the final write-up of the trial where there is no risk of a confidentiality breach.

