#### Aims and objectives

The primary aim is to conduct a randomised waitlist-controlled feasibility trial of a lifestyle intervention (Motiv8) + TAU for adults in secure mental health units, to investigate the acceptability, feasibility and potential effectiveness of this intervention to supplement standard secure care (see Table 1).

**Table 1 Tab1:** Aims, objectives and outcomes

Research question/aim(s)	Objectives	Outcomes
Primary	To assess the acceptability and feasibility of the research trial, associated processes including the intervention, and assessments	Measured by: - Recruitment rates - Follow-up retention and questionnaire/outcome response rates - Attendance at sessions - Experience of involvement in the trial - Assessment of safety (SAEs) - Development of a manualised intervention
Secondary	Physical Health: Body composition, blood pressure, cardiovascular fitness, health status Mental Health: Wellbeing, depression, anxiety, negative symptoms Behavioural: Physical activity, occupational functioning, diet, sleep	Physical health measures: - BMI - BP - Hip/waist/chest/neck circumference - Fitness test Mental health measures: - WEMWBS - HADS - SNS Behavioural measures: - SIMPAQ - MOHOST - 24-h diet recall - PROMIS SD Short-Form - PROMIS SRI Short Form Measures to support economic evaluation: - EQ-5D-5L - ReQoL - Engagement in care - LUNSERS - Ward activity
Tertiary	Clarify training needs for delivering Motiv8 via a MDT care team, prior to the commencement of a definitive trial	- Qualitative interview - Adherence checklists - Feedback forms and interviews with facilitators - M-BacK Assessment and ESSEN-CES with clinical staff

*BMI* body max index, *BP* blood pressure, *ESSEN-CES* ESSEN Climate Evaluation Schema, *HADS* Hospital Anxiety and Depression Scale, *LUNSERS* Liverpool University Neuroleptic Side Effect Rating Scale, *M-Back* Metabolic-Barriers, Attitudes, Confidence and Knowledge Questionnaire, *MDT* multi-disciplinary team, *MOHOST* Model Of Human Occupation Screening Tool, *PROMIS SD* Patient Reported Outcome Measurement Information Centre Sleep Disturbance, *PROMIS SRI* Patient Reported Outcome Measurement Information Centre Sleep-Related Impairment, *ReQoL* Recovering Quality of Life, *SAEs* Serious Adverse Event, *SIMPAQ* Simple Physical Activity Questionnaire, *SNS* Self-evaluation of Negative Symptoms, *WEMWBS* Warwick Edinburgh Mental Wellbeing Scale

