### Randomisation and blinding

Individuals will be cluster randomised by cohort, using minimisation to ensure balanced distribution. Following written consent, cohorts will be randomised using a free web-based system (www.sealedenvelope.com). Allocation will be communicated to the CI, study management team and facilitators but not research assistants, statistician or health economist. Participants will be informed of their randomisation status by letter or via clinicians, communicated via the administrator.

Blinding of allocation will be maintained for research assistants until all outcome measures for all subjects have been collected. Blindness will be maintained using a range of measures (e.g. separate offices for facilitators and researchers, protocols for answering phones, secretarial support). Unblinding will be communicated to the CI, and if possible, future assessments will be conducted by a blinded assessor. This may not always be possible due to the trial being cluster randomised, and therefore unblinding will occur on a cohort basis. Maintaining rater blindness to treatment allocation is crucial, and the TSC will be consulted in the instance that any unblinding occurs and implement corrective action if necessary.

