### Analysis

A detailed Statistical Analysis Plan will be drafted by the study statistician prior to data analysis and a Health Economics Analysis Plan will be drafted by the study health economist. Quantitative analysis will be conducted according to intention-to-treat and reported according to CONSORT guidelines for cluster randomised pilot and feasibility studies [46], including the numbers of prospective participants who were approached, deemed eligible and consented. The number of participants who received their intended treatment (including which elements of it) will be reported.

There are no formal stopping rules for this study as the primary aim is to assess feasibility. The primary focus will be on tabulated and graphical summaries of key indicators of success of the study, e.g. recruitment, engagement, retention and satisfaction with the Motiv8 intervention (participant and facilitator). Where applicable these will be reported with a 95% confidence interval. All adverse events will be reported. We will summarise the baseline demographic and clinical characteristics of each cohort by trial arm. The completion rate of assessments will be reported, as well as descriptive characteristics such as mean (SD), median (IQR) or number (percentage).

To determine the potential utility of the Motiv8 intervention, an appropriate regression model will be fit to the data, using our intended primary outcome (weight), with a trial arm as a covariate controlling for gender and ward type. *P*-values will not be reported as this study is not designed to test effectiveness—instead, 70, 80 and 90% confidence intervals for the difference in weight between Motiv8 and TAU. Alternative proposed primary outcomes such as cardiovascular fitness, physical activity and well-being will be explored.

As Motiv8 is delivered in cohorts, a degree of intra-cohort correlation will exist in the outcomes. A sample size calculation for a definitive trial will require an estimate of the intra-cohort correlation. The correlation in this study will be investigated, but the number of cohorts is likely to be too small to obtain an accurate estimate. We will use descriptive statistics to inform the design of the economic components of the definitive trial, based on completion rate and summaries of relevant data (ReQOL, EQ-5D, service use and engagement, treatments).

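### SAEs found only in the end-of-study notes review are recorded subject to a relevance judgement, so the SAE count will be incomplete and conflicts with the promise to report all adverse events

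*Protocol article*

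**What the plan says.** The Adverse events section describes two ways in which an SAE can enter the trial record.

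- **Reported SAEs.** A standard operating procedure exists to "ensure all SAEs which are reported to the research team are assessed and categorised in line with HRA requirements". The research team, the Trial Steering Committee (TSC) and the experts by experience group are told of SAEs and "will determine whether they are related to participation in the trial". Here relatedness is assessed after the event is already known, and recording carries no relevance condition.
- **SAEs found in the notes.** "Clinical notes will be reviewed at the end of the study period and any SAEs will be recorded if deemed relevant to participation". Here the relevance judgement decides whether the event is recorded. The section does not say who makes it.

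The same section warns that "SAEs are expected throughout the study period, such as incidents of self-harm, or violence and aggression". On publication it says: "Adverse events will be reported in the final write-up of the trial where there is no risk of a confidentiality breach".

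Elsewhere, Table 1 (Aims and objectives) places safety, measured by SAEs, among the primary outcomes, and the Analysis section states without qualification: "All adverse events will be reported". On knowledge of allocation, Randomisation and blinding says: "Allocation will be communicated to the CI, study management team and facilitators but not research assistants, statistician or health economist". Under Waitlist control group, the control participants receive Motiv8 after the 10-week assessment.

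**The concern.** Recording and attribution are separate steps. If an event must be judged relevant before it is written down, the data set holds only the events that someone has already attributed to the trial, and the background is lost. In this population the background matters: self-harm and violence are expected whatever the treatment. A definitive trial would be planned from these data, and it needs to know how often SAEs occur in this setting as well as how often they were thought to be caused by taking part.

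Two things are at stake. The main one is completeness of a listed primary feasibility outcome. Events that were never recorded cannot be recovered by any analysis plan, so this cannot be left to the SAP. The second is comparability. During the first 10 weeks a waitlist participant's involvement consists of assessments and waiting, while a Motiv8 participant attends a full programme. The same incident may be linked to taking part more readily in the second case than in the first. If so, the filter would remove more control events than Motiv8 events.

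**Working it through.** The article gives no SAE rate, safety threshold or power statement for safety, so there is no figure of its own to reproduce on this point. The check is mainly textual.

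**Step 1: the two sections side by side.** Analysis commits to reporting all adverse events. Adverse events makes recording of note-identified SAEs conditional on relevance. An SAE in the notes that is judged not relevant is not recorded, and an unrecorded event cannot be reported. As soon as one such event occurs, both statements cannot be met.

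**Step 2: does the other route close the gap?** Only for SAEs that reach the research team. The article describes no systematic search behind that route, and the chance of being noticed may differ by arm. The example schedule in Table 2 has 26 exercise sessions (2 + 8 × 3), 8 diet sessions and 3 psychology sessions over nine weeks, so facilitators see Motiv8 participants several times a week. Waitlist participants have usual care and assessments. The notes review is the one described source that could cover both arms evenly, and it is the source with the filter.

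**Step 3: illustration of size (all rates assumed).**

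Inputs:
- n = 16 per arm: four cohorts of eight (4 × 8 = 32, as stated), assuming that they split two and two.
- p = true proportion with an SAE, set equal in both arms.
- q = probability that an affected participant's SAE is judged relevant, by arm.
- Every SAE is assumed to be known only from the notes.

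Formulas:
- Recorded per arm = n × p × q.
- Spurious risk difference = p × (q_Motiv8 − q_control).
- Chance of no recorded control case = (1 − p × q_control)^16, treating participants as independent.

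| p | true per arm | q Motiv8 | q control | recorded Motiv8 | recorded control | spurious difference (points) | chance of no control case |
|---|---|---|---|---|---|---|---|
| 0.3 | 4.8 | 1 | 1 | 4.8 | 4.8 | 0 | 0.3% |
| 0.3 | 4.8 | 0.5 | 0.5 | 2.4 | 2.4 | 0 | 7.4% |
| 0.3 | 4.8 | 0.5 | 0.25 | 2.4 | 1.2 | 7.5 | 28.7% |
| 0.3 | 4.8 | 0.5 | 0.05 | 2.4 | 0.24 | 13.5 | 78.5% |
| 0.1 | 1.6 | 0.5 | 0.05 | 0.8 | 0.08 | 4.5 | 92.3% |
| 0.5 | 8.0 | 0.5 | 0.05 | 4.0 | 0.4 | 22.5 | 66.7% |

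For the fourth row: 16 × 0.3 × 0.5 = 2.4; 16 × 0.3 × 0.05 = 0.24; 0.3 × (0.5 − 0.05) = 0.135; (1 − 0.015)^16 = 0.785.

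**Step 4: reading the table.** The second row does not depend on any difference between arms: with equal filtering there is no spurious contrast, but half of the affected participants are missing. The later rows show a false excess in Motiv8 only because q is assumed to be lower in the control arm. All losses shrink in proportion to the share of SAEs known only from the notes, and vanish if the reporting route captures everything. The first row is the position after the fix: q = 1 in both arms, nothing lost, no spurious difference.

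**The case against.** Several points can fairly be made for the plan.

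- **The filter covers one route only.** SAEs reported to the research team are assessed without a relevance condition, and how many would surface only in the notes is unknown. The operating procedure is not shown and may define relevance. This stands, and it limits the point to the notes review. It does not remove the conflict with the Analysis section.
- **An unblinded judgement is not documented.** A reader might infer one, because the research team helps to decide relatedness and the chief investigator and management team know the allocation. But no judge is named for the notes review, research assistants are kept blind until outcome collection is complete, and the blinding status of the TSC and the experts by experience group is not given. That blinding may have lapsed by the end of the study, and judging relevance may in practice require knowing who was receiving Motiv8. These are reasons for concern, not evidence of what will happen.
- **A near-empty control arm is not documented.** A reader might also infer that almost no waitlist SAE would be recorded. That needs q near zero in the control arm and little contribution from the reporting route. The relatedness wording concerns participation in the trial, and waitlist participants are assessed and do physical tests. They also receive Motiv8 after 10 weeks, so any differential from being untreated is confined to that first period.
- **No between-arm SAE test is planned.** There are no formal stopping rules and no safety progression criterion. Even complete counts would be imprecise: at 4 of 16 in each arm, the 95% Wald half-width is 1.96 × √(2 × 0.25 × 0.75 / 16) = 0.30, or 30 points, before any allowance for clustering. This stands: the harm is mainly to complete description, and complete counts would not settle whether Motiv8 changes the SAE rate.
- **The confidentiality sentence is reasonable.** With 32 forensic inpatients in one trust, withholding identifying detail is proper, and the sentence can be read that way. It is loosely worded, but it is not clear permission to drop events.

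**Conclusion.** The point holds in a limited form. For SAEs found only in the notes, the Adverse events section makes recording depend on a causal judgement. That contradicts the Analysis section and leaves a listed primary feasibility outcome incomplete whenever such an event is judged not relevant. This follows from a rule that the article states, not from something it leaves out.

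The size cannot be fixed from the article. If every SAE were known only from the notes and half were judged relevant in both arms, half of the affected participants would be missing. If relevance were judged at 0.5 in Motiv8 and 0.05 in the control arm, equal true risks of 0.1 to 0.5 would appear as a difference of 4.5 to 22.5 points. These figures rest entirely on assumed values. Differential loss is a risk, and neither an unblinded filter nor an emptied control arm is established.

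This should be fixed. It is not critical to the trial, because no stated estimate, stopping rule or progression criterion depends on the filtered count.

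**What to change.** In the notes review already planned:

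- Record every SAE for every participant from consent to last assessment, whatever its relatedness.
- Hold relatedness as a separate field, and state who completes it and whether they know the allocation.
- Tabulate SAEs by arm and by period: waitlist/TAU, during Motiv8, after Motiv8.
- Report all events, in aggregate where detail could identify someone, and reword the confidentiality sentence to say so.
- Reconcile the Adverse events and Analysis sections so that both state the same rule.

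The cost is a little more data entry and a wording change, including in the operating procedure. The notes are being reviewed in any case.

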### Trial status

The trial begun recruitment in December 2021. Recruitment will occur in two stages (to allow recruitment of the four clusters on a ward-by-ward basis) and will be complete by approximately July 2022 for the main cohort. The staff sub-study begun recruitment in December 2021. The study has been granted an extension to September 2023. Final outcome data will be collected by August 2023 and analysis completed by September 2023. A trial paper with outcomes is expected to be submitted for publication by January 2024.

## Data Availability

Not applicable. A full dataset is not yet available for this work and data sharing is not yet available.
